# STATISTICAL CONSIDERATIONS

## Population for analyses

12.1.1 Safety Data Set. All participants enrolled in the trial will be eligible for the safety data set. AEs and suicidality per C-SSRS will be assessed across both study arms.

12.1.2. Evaluable for intent-to-treat (ITT) analysis. All participants enrolled in the trial and randomized to either MBSR + PAP or MBSR only will be eligible for the (ITT) analysis. The primary analysis will involve intention to treat analyses on all study outcomes.

12.1.2 Evaluable for per-protocol analysis. Participants in the MBSR arm who have completed two-thirds of the MBSR sessions will be considered evaluable for the per-protocol efficacy data set. Participants in the MBSR + PAP arm who have completed two- thirds of the MBSR sessions (excepting the MBSR retreat) *as well as* two out of three of the preparatory sessions, the psilocybin therapy session, two out of the three integration sessions, and a baseline and post-psilocybin QIDS-SR and MBI will be considered evaluable for the per-protocol efficacy data set.

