# TREATMENT PLAN

## Treatment Schedule

### MBSR Arm

Participants randomized to the MBSR only arm will be enrolled in the MBSR curriculum led by [name] LCSW through the University of Utah Resiliency Center. Cost for University of Utah employees ($99) will be covered through the study. If capacity limits the feasibility of running this internally we will consider utilizing MBSR groups through Intermountain as well as Davis Behavioral Health and this cost ($250 per participant) will be covered through the study. Mindfulness-Based Stress Reduction, (MBSR), was developed by Jon Kabat-Zinn at the Center for Mindfulness, University of Massachusetts Medical School. MBSR is an intensive training in developing mindful awareness and accessing our innate capacity for health, healing and growth. Groups meet for an orientation, 9 weekly classes and an all-day retreat held in the final two weeks of the curriculum Guided instruction in various practices is provided, including sitting and walking meditation, body scan, gentle yoga, and mindful communication. These practices are enhanced through inquiry exercises, group dialogue, and daily home assignments.

MBSR has been shown to be an effective ameliorative measure for healthcare related burnout (Cohen-Katz, 2005) independent of PAP. Given this, we believe it will be an ideal active comparator to the novel administration of psilocybin in this population.

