### MBSR+PAP Arm

Participants randomized to the MBSR + PAP arm will participate in the same curriculum as described above, however, will substitute a group PAP session instead of the group MBSR retreat. The PAP intervention will be facilitated with a 1:1 therapist/participant ratio with an additional lead therapist. Group size will be determined by ease of recruitment but will be no fewer than 2, and no more than 6 participants per PAP session. The group will be overseen by a lead therapist who will be available through the entirety of the dosing session and will not be assigned to any one individual participant. Timing of the PAP session will be during the MBSR curriculum with a goal of scheduling at same time as the MBSR retreat for the other arm. However, scheduling will be flexible depending on participant schedules, particularly given working demands of healthcare providers amid a pandemic: this session may occur before or after the group meditation retreat +/- 1 week. The psilocybin session will be accompanied by 3 preceding group preparatory sessions of 90 minutes each (one of these can be via Zoom per participant) as well as 3 integration sessions of 90 minutes each (up to two of these can be via Zoom per participant). Participants must continue to meet all inclusion criteria as well as hepatic and renal function requirements laid out in inclusion and exclusion criteria to receive psilocybin.

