## Duration of Therapy

*MBSR arm*: Total duration of the MBSR curriculum is 8 weeks with a once weekly session (over Zoom or in person) for 2 hours and a full day mindfulness retreat.

*MBSR + PAP arm*: Total duration is the same as above for the MBSR curriculum with a 9 week total duration (given additional integration session following MBSR completion). This arm will include an additional time to incorporate the PAP protocol. This includes three 90min preparatory sessions, one 8 hour psilocybin session (in place of the MBSR retreat), and three 90 minute integration sessions.

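### The per-protocol set in Protocol 12.1 requires the full-day session and outcome data in the MBSR + PAP arm but neither in the MBSR arm, so the two arms are selected differently

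*Protocol*

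**What the plan says.** Protocol 12.1 (Population for analyses) writes a separate per-protocol rule for each arm.

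- **MBSR arm:** "Participants in the MBSR arm who have completed two-thirds of the MBSR sessions will be considered evaluable for the per-protocol efficacy data set". No other condition is given.
- **MBSR + PAP arm:** the attendance rule opens with "Participants in the MBSR + PAP arm who have completed two- thirds of the MBSR sessions (excepting the MBSR retreat"). On top of this come the components that only this arm has: "two out of three of the preparatory sessions, the psilocybin therapy session, two out of the three integration sessions". A further condition concerns scores on the two main scales, and the rule closes with it: "and a baseline and post-psilocybin QIDS-SR and MBI will be considered evaluable for the per-protocol efficacy data set".

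The retreat and the psilocybin day are counterparts. Section 6.1 (MBSR+PAP Arm) says that this arm "will substitute a group PAP session instead of the group MBSR retreat", and section 4.1 says the same.

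The number of sessions of which two-thirds is taken is not fixed. Section 6.4 states "Total duration of the MBSR curriculum is 8 weeks with a once weekly session", and section 4.1 and Table 2 agree on eight. Section 6.1 (MBSR Arm) states "Groups meet for an orientation, 9 weekly classes and an all-day retreat held in the final two weeks of the curriculum", and section 9.3 repeats the nine.

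On the status of the set, 12.1 says: "The primary analysis will involve intention to treat analyses on all study outcomes".

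**The concern.** Take two participants with the same record: six weekly classes attended, the full-day component missed, no follow-up QIDS-SR or MBI. Under 12.1 the one in the MBSR arm is in the per-protocol efficacy set and the one in the MBSR + PAP arm is out. The outcome-data clause cannot be read as covering both arms, because a post-psilocybin score can exist only where psilocybin was given.

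If people who complete more steps also tend to improve more, filtering one arm harder shifts the contrast toward that arm. The protocol also contains one route by which exclusion could follow from outcome. Regular antidepressant or anxiolytic use bars dosing in the psilocybin arm (sections 5.1, 5.2 and 6.1). Someone who worsens and starts such a drug before the dosing day would miss dosing and leave the set, while an MBSR participant with the same course would stay.

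At stake is whether a per-protocol estimate that agrees with or exceeds the intention-to-treat estimate can be read as support for it.

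**Working it through.** The protocol states no expected size for the per-protocol set, so there is no figure to reproduce. Everything in steps 2 to 4 is illustration on assumed inputs. The only input from the protocol, besides the rule itself, is 12 participants per arm (section 4.2).

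**1. Threshold.** Two-thirds, rounded up:
- 8 sessions: 5.33, so 6
- 9 sessions: 6
- 10 sessions: 6.67, so 7
- 11 sessions: 7.33, so 8

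Eight weekly classes give 6 with or without the retreat. Nine classes alone also give 6. Only nine classes plus the retreat, the orientation, or both give 7 or 8. The retreat is set aside explicitly for the MBSR + PAP arm only, so it could count as an ordinary session in the other arm.

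**2. Inclusion.** Assume each session is attended independently with probability a.
- MBSR: M = P(Bin(8, a) ≥ 6)
- Two of three sessions: S = P(Bin(3, a) ≥ 2)
- MBSR + PAP: M × S² × d, with d the probability of attending the dosing day, before the outcome-data condition

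| a | M | S² | MBSR + PAP, d = a | MBSR + PAP, d = 1 | MBSR if retreat required (M × a) |
|---|---|---|---|---|---|
| 0.80 | 0.797 | 0.803 | 0.512 | 0.640 | 0.638 |
| 0.85 | 0.895 | 0.882 | 0.671 | 0.789 | 0.761 |
| 0.90 | 0.962 | 0.945 | 0.818 | 0.909 | 0.866 |

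At a = 0.85 with d = a this is 12 × 0.895 = 10.7 against 12 × 0.671 = 8.1 participants. If the retreat counts as a ninth session in the MBSR arm (6 of 9), M becomes 0.914, 0.966 and 0.992. At a = 0.70, M is only 0.552 (0.730 for 6 of 9).

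**3. Bias, upper bound.** Suppose inclusion were perfect truncation on an adherence trait that correlates r = 0.2–0.4 with improvement. The mean trait among the retained share p is φ(z)/p, where z is the cut-off that retains p.
- a = 0.80: 0.355 (MBSR) and 0.779 (MBSR + PAP), difference about 0.425. Times 0.4 is 0.17 SD.
- a = 0.90: 0.086 and 0.323, difference 0.237. Times 0.2 is 0.05 SD.

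The range is 0.05–0.17 SD. It joins two models that do not fit together: the shares come from independent attendance, which carries no trait, and the bias treats those shares as pure trait selection. Hence it is a ceiling for these inputs. Lower attendance, or counting the retreat as a session, would raise it.

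**4. Bias, one consistent model.** Let each person have an own attendance probability p, beta-distributed with mean 0.80–0.90 and within-person correlation 0.1–0.5. Weight the standardised p by M(p) in the MBSR arm and by M(p) × S(p)² × p in the MBSR + PAP arm. The mean trait then differs between the sets by 0.05–0.20 SD. Times r = 0.2–0.4 this gives about 0.01–0.08 SD. At mean 0.85 and correlation 0.3, inclusion is 81% against 71%.

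**5. Scale.** With 12 per arm the standard error of a standardised difference is about √(2/12) = 0.41 SD.

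**6. Outcome-data condition.** In one simulated 24-person example of the mixed model, four MBSR participants with baseline only were kept and then removed. The Treatment × Time estimate was −0.39 (SE 0.51) and −0.43 (SE 0.52). Such participants carry almost no information on the contrast.

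**The case against.** The strongest reply is that nothing important rests on this set. Intention-to-treat is primary for all outcomes, and 12.2 with its Primary and Secondary Analysis parts attaches no named analysis to the per-protocol set. The study is a pilot meant to estimate effect sizes and feasibility, and a bias of this order is well below half a standard error. That stands, and it limits the point to a supportive analysis.

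Part of the asymmetry is also inherent. Preparatory and integration sessions exist in one arm only, and a participant who was never dosed has not received the experimental treatment. That stands too, but it does not explain why the retreat and the outcome scores are left out on the other side.

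Three stronger readings are tempting and not supported:

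- A reader might infer that the rule compares selected completers with nearly all MBSR participants. The MBSR arm still has its two-thirds filter. Nearly all would pass only at about 90% attendance or more, or about 80% if the retreat counts as a session, and the protocol gives no attendance figure.
- A reader might infer that the MBSR + PAP arm must have complete outcome data. The rule asks only for a baseline and a post-psilocybin QIDS-SR and MBI, not the 6-month visit or the other scales.
- A reader might take 0.17 SD as the expected bias and set it against the assumed d = 1.0. It is the extreme of step 3, and neither attendance nor the link between adherence and outcome is documented. The inclusion gap also depends on the dosing day being missed as often as a weekly class. If all attend it, 90% attendance gives 96% against 91%.

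**Conclusion.** The point holds as a defect in the stated definition. Section 12.1 holds the arms to different standards on two matters where they could be alike: the full-day component and outcome data. The missing retreat condition matters more, because baseline-only participants hardly affect the contrast. In every scenario examined the MBSR + PAP set is the more selected one, so any tilt is toward that arm. Its size cannot be read from the protocol. On assumed attendance of 80–90% and an assumed correlation of 0.2–0.4 it is probably below 0.1 SD, with about 0.17 SD as the upper bound on those inputs. The primary intention-to-treat analysis is untouched.

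**What to change.** Rewrite the per-protocol definition in 12.1 so that both arms meet the same conditions:

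- the same two-thirds threshold on the weekly MBSR classes, with retreat and orientation counted in neither arm;
- attendance at the arm's full-day component, that is, the retreat or the psilocybin session;
- a baseline and a 2-week post-intervention QIDS-SR-16 and MBI, in place of the post-psilocybin wording. Name the visit in this way and not by week number: the Schedule of Events note counts 14 days from the final week 8 session, whereas the Primary Analysis part counts from each arm's last session.

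Keep the preparatory and integration conditions as the only ones specific to MBSR + PAP.

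Two contradictions must be reconciled at the same time. The number of weekly classes (eight in 4.1, 6.4 and Table 2; nine in 6.1 and 9.3) must be settled so that the threshold is one fixed count. The two-thirds tolerance must also be squared with the discontinuation criteria under 6.4, where missing any MBSR or PAP session counts as non-compliance and ends study treatment.

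The cost is protocol wording and a slightly smaller MBSR per-protocol set: at 85% attendance, requiring the retreat takes MBSR inclusion from 89% to 76%, against 67% in MBSR + PAP. The remaining gap comes from the sessions that only one arm has. The medication route described above is not removed, so reasons for exclusion should be reported by arm.

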## Statistical Analyses

Aim 1 is to assess the safety and feasibility of MSBR and PAP for burnout. We will track frequency and percentage of adverse events and rates of serious adverse events utilizing the Common Terminology Criteria for Adverse Events (CTCAE) v.5 from study initiation until termination, as well as the Columbia Suicide Severity Rating Scale (C-SSRS). We will also track qualitative data from participant and clinician direct reporting as well as outcomes with the Challenging Experience Questionnaire (ChEQ).

Aim 2 is to assess the efficacy of MBSR+PAP vs. MBSR alone in reducing symptoms of depression, burnout, demoralization, and other clinical symptoms. For continuous outcomes, the analysis will be performed under a generalized linear mixed model (GLMM). The model will include follow-up time as a categorical predictor variable (baseline, 2 weeks, 6 months) as well as the interaction of this categorical factor with the randomized treatment group. Our primary interest lies in the Treatment X Time interaction, expressible as a linear contrast on the β parameters. Repeated effects will incorporate autoregressive dimensioning of the linear predictor, if needed and supported by the Bayesian Information Criterion. In the case that pre-randomization between-groups differences are present in the baseline values of outcome variables, effects will be controlled for chance baseline imbalance using an analysis of covariance strategy that conditions on baseline values. We will use maximum likelihood estimation of missing data for intent-to-treat analyses of all study outcomes.

The statistical model is expressed mathematically as below:

$$Y_{it}=\alpha_{00}+{\alpha_{10}Trt}_{i}+{\alpha_{20}Time1}_{it}+{\alpha_{21}Time2}_{it}+$$

$${\alpha_{30}Trt}_{i}{Time1}_{it}+{\alpha_{31}Trt}_{i}{Time2}_{it}+Z_{i}\beta_{i}+\epsilon_{ijt},$$

$$\beta_{i}\sim N\left( 0, \psi^{2} \right) \left( EQ1 \right)$$

$\epsilon_{it}\sim N\left( 0, \phi^{2}\lambda_{itt} \right), Cov\left( \epsilon_{it}, \epsilon_{it^{'}} \right)=\phi^{2}\lambda_{itt'}$

In EQ1, $Y_{it}$ denotes the continuous outcome measure for depression or burnout score measured at the $t^{th}$time (t=0, 1, 2 for baseline, 2^nd^ week and 6^th^ month) for the $i^{th}$ participant, $\alpha_{00}$ is the intercept, which is the effect for the MBSR alone group at baseline, $\alpha_{10}$ is the treatment effect difference between MBSR+PAP vs. MBSR alone group at baseline, ${Trt}_{i}$ is a 0-1 indicator variable which takes the value 1 when the $i^{th}$ participant is assigned to the MBSR+PAP group, otherwise 0, $\alpha_{20}$ is the difference between the 2^nd^ week and baseline for MBSR alone group, $\alpha_{21}$ is the difference between the 6^th^ month and baseline for MBSR alone group, ${Time1}_{it}$ and ${Time2}_{it}$ are 0-1 indicator variables which take the value 1 when t=1 (2^nd^ week), t=2 (6^th^ month, $\alpha_{30}$ is the extra treatment effect difference between MBSR+PAP and MBSR alone group when compare the 2^nd^ week to baseline, $\alpha_{31}$ is the extra treatment effect difference between MBSR+PAP and MBSR alone group when compare the 6^th^ month to baseline, $Z_{i}$is a 0-1 indicator variable which take the value 1 for the $i^{th}$ participant, otherwise 0, $\beta_{i}$ is the participant effect for the $i^{th}$ participant, $\psi^{2}$is the variance of the random participant effect ($\beta_{i}$), $\epsilon_{it}$ is the residual at the $t^{th}$time for the $i^{th}$ participant, $\phi^{2}\lambda_{itt'}$ is the covariance between the $t^{th}$ and the ${t'}^{th}$time.

The coefficient of $\alpha_{30}$ is the difference of reduction in depression/burnout from baseline to the 2^nd^ week comparing the two groups, which constitutes the efficacy of the MBSR+PAP. The coefficient of $\alpha_{31}$ are the difference from baseline to the 6^th^ month, which constitutes the long-term effect of the outcome. For outcomes with only two timepoints, the coefficient of $\alpha_{31}$ will be dropped.

In an exploratory analysis, burnout measured as a binary variable (e.g., burnout vs. not-burnout) will be evaluated using generalized linear mixed effects models assuming a binomial distribution with probit (cumulative logistic) link. The probit link gives results very similar to the logit link, but yields a more natural interpretation in terms of an underlying propensity.

We will also assess the correlation between magnitude of change in burnout scores on the MBI using Pearson correlation. Path analysis will be used to assess changes in the Mystical Experience Questionnaire (MEQ-30), Challenging Experience Questionnaire, and Nondual Awareness Dimensional Assessment (NADA) as mediators of the effect of treatment (MBSR+PAP vs MBSR alone) on burnout, using bootstrapping to assess the significance of the indirect effect (Preacher & Hayes, 2008).

### Statistical Power

### Power is based on the efficacy of MBSR+PAP vs. MBSR alone in reducing symptoms of depression. A meta-analysis examining the effects of psilocybin on depressive symptoms reported an effect size of Cohen’s d=1.29. Previous meta-analyses of MBSR indicate modest to moderate effect sizes for depressive symptom reduction (Cohen’s d= 0.3 to 0.4). We conducted simulation-based power calculations for the linear mixed-effects model. Assuming a **large between group effect size (Cohen’s d = 1.0)**, alpha=0.05, and a **moderate-to-high intra-class correlation (ICC = 0.5)**reflecting the repeated measures design, the estimated power to detect a **treatment group × time interaction** in the LMM was approximately **81%**. Given the pilot nature of this study, the primary goal was to estimate effect sizes and assess feasibility to inform future larger-scale trials.

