# STUDY SUMMARY

| Title | PAPR: Psilocybin-assisted psychotherapy (PAP) + Mindfulness-based Stress Reduction (MBSR) for front-line healthcare provider COVID-related depression and burnout. |
| --- | --- |
| Short Title | PAPR |
| Protocol Identifiers (IRB – internal) |  |
| IND number | 163040 |
| Phase | Pilot |
| Design | Open-label, pilot trial. |
| Study Duration | 1.0 years |
| Study Center(s) | This is a single-center trial to be conducted at Huntsman Mental Health Institute |
| Objectives | **Primary Objectives**   - To assess the safety and tolerability of psilocybin in the study population. - To assess the feasibility to recruit, consent, and enroll healthcare providers in a study of psilocybin-assisted therapy + MBSR vs. MBSR and for those participants to remain in the study until completion. - To assess the effect that psilocybin-assisted therapy has on depression symptoms in healthcare providers with burnout as measured by the QIDS-SR-16.   **Secondary Objectives**   - To assess the changes in rates of provider burnout as measured by the Maslach Burnout Inventory for Medical Professionals (MBI-HSS (MP)) both in terms of rates of meeting criteria for burnout as well as mean reduction in score on the MBI. - To assess the long-term effect that psilocybin-assisted therapy and MBSR have on depression and anxiety symptoms in the study population. - To assess the effect psilocybin therapy and MBSR have on symptoms of post-traumatic stress syndrome. - To assess the effect psilocybin therapy and MBSR have on participant reported quality of life. - To assess the effect psilocybin therapy and MBSR have on participant reported feelings of connectedeness to self, other, and world.   **Exploratory Objectives**   - To assess the effect psilocybin therapy, in conjunction with an MBSR curriculum, has on state and trait mindfulness measures. - To assess participant-reported psilocybin experience on the day of medication administration and to assess the relationship between reported experience and depression and burnout response. - To use the Storyline Health AI platform to develop a model for precision research on psychedelic-assisted therapies and healthcare provider burnout and to better characterize predictors of response to mindfulness training and psilocybin therapy utilizing the Storyline Integrative Assessment tool. |
| Number of Subjects | 25 |

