| Diagnosis and Main Eligibility Criteria | **Key Inclusion Criteria:**   - Male or female healthcare providers aged ≥ 25 years old. - Participants must be physicians or nurses with at least 1 month of frontline clinical experience during the COVID-19 pandemic. - Screening MBI-HSS (MP) score that meets our working definition of burnout (emotional exhaustion subscale ≥ 27) and a ‘high’ score on one other subscale (either depersonalization ≥ 13 or personal accomplishment ≤ 21). - PHQ-9 depression screen ≥ 10. - Not taking regularly scheduled medications to treat depression and/or anxiety, including benzodiazepines, for at least 4 weeks prior to initiation of the study.   **Key Exclusion Criteria:**   - Prior systemic antidepressants, anti-psychotic, or anxiolytic medication within four weeks prior to psilocybin administration. - Personal history or immediate family members with schizophrenia, bipolar affective disorder, delusional disorder, schizoaffective disorder, psychosis, dementia, or other psychotic spectrum illness. - Currently meeting DSM-5 criteria for Dissociative Disorder, or other psychiatric conditions judged to be incompatible with the establishment of rapport or safe exposure to psilocybin. - Currently meeting DSM-5 criteria for Cluster B Personality Disorder). - Current or history within the last two years of meeting DSM-5 criteria of substance use disorder (excluding caffeine and nicotine). |
| Study Product, Dose, Route, Regimen | Psilocybin 25 mg PO |
| Duration of administration | One-time administration |
| Reference therapy | MBSR |
| Statistical Methodology | Feasibility will be assessed by the ability to recruit, consent, and enroll 24 patients in the trial, and for at least 16/24 patients to remain in the study until completion.  The key secondary analysis of QIDS-SR-16 and MBI-HSS(MP) will use mixed-effects models with fixed effects for time (enrollment, 2 weeks post psilocybin), and a random intercept term. The outcome variables are the estimated change from baseline to 2 weeks post psilocybin from these models. |

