## Number of Patients

This study will enroll a total of 24 patients with 12 patients in each study arm.

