### Sample size determination:

QIDS-SR-16: Prior studies that have utilized depression rating scales (HAM-D) (Griffiths et al. 2016) have reported within-group effect sizes of 1.30 and 1.23, respectively (with cancer patients with depression and anxiety symptoms). This was with an 82% completion rate of randomized subjects. Additionally, 4 small studies looking at pre-post measures of depression with a psilocybin-assisted therapy intervention (N=69) have demonstrated a pooled standardized effect size of Hedges g 1.38 (Goldberg 2020).

Determining sample size in relation to the MBI and symptoms of burnout is more difficult given less precedent in the literature. Demoralization is a closely related and overlapping concept and Anderson et al. (2020) investigated response to demoralization (Demoralization II Scale) in a psilocybin-assisted group intervention with patients with AIDS. This study demonstrated an effect size (Cohen’s d) of 0.97. Using this effect size and an alpha of 0.05, a sample size of 18 patients would provide 80% power to detect this difference between groups.

We conducted simulation-based power calculations for the linear mixed-effects model. Assuming a **large between group effect size (Cohen’s d = 1.0)**, alpha=0.05, and a **moderate-to-high intra-class correlation (ICC = 0.5)**reflecting the repeated measures design, the estimated power to detect a **treatment group × time interaction** in the LMM was approximately **81%**. Given the pilot nature of this study, the primary goal was to estimate effect sizes and assess feasibility to inform future larger-scale trials.

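### The stated 81% power does not describe the baseline-to-2-week comparison at 12 per arm (about 65%), and the 18 patients given for 80% power is a per-group number

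*Protocol*

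**What the plan says.** The subsections of 12.2 on Statistical Power and on Sample size determination carry the same statement. The inputs are given as "Assuming a large between group effect size (Cohen’s d = 1.0), alpha=0.05" and a "moderate-to-high intra-class correlation (ICC = 0.5)reflecting the repeated measures design". The result is that "the estimated power to detect a treatment group × time interaction in the LMM was approximately 81" per cent. The statement gives no N, sidedness, visit coding or allowance for loss.

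The test is described earlier in 12.2: "Our primary interest lies in the Treatment X Time interaction, expressible as a linear contrast on the β parameters". The explanation of EQ1 then assigns efficacy to α30, the between-arm difference in change from baseline to 2 weeks. The 6-month coefficient, α31, is described as the long-term effect. EQ1 has a separate term for a baseline difference between arms (α10), and adjustment for baseline is planned only if the arms differ at baseline.

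For burnout, Sample size determination takes d = 0.97 and states that "a sample size of 18 patients would provide 80% power to detect this difference between groups".

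On size, section 4.2 says: "This study will enroll a total of 24 patients with 12 patients in each study arm". The Study Summary table has "Number of Subjects | 25", while its Statistical Methodology row counts 24 and asks "for at least 16/24 patients to remain in the study until completion".

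**The concern.** With 12 per arm and a standardised difference of 1.0, a two-arm comparison of change scores does not normally reach 80% power, so 81% looked too high. The two sizing statements also do not fit together. If d = 0.97 needs 18 per group for 80%, then d = 1.0 cannot give 81% with 12 per group in the same kind of comparison.

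At stake is what readers of the protocol believe about a primary endpoint. The between-group QIDS-SR-16 comparison at 2 weeks is listed as primary in section 1.1. At 81% the chance of missing a true d = 1.0 is about 1 in 5; at 65% it is about 1 in 3. The burnout sentence has a further effect. As printed, 24 participants seem to exceed a requirement of 18, whereas read correctly the requirement is 36 and the plan falls short of it.

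**Working it through.** **Inputs.** d = 1.0, alpha 0.05, ICC = 0.5 (12.2, Statistical Power); 12 per arm (4.2); contrast α30 (12.2, explanation of EQ1); d = 0.97 and 18 patients (12.2, Sample size determination). Sidedness is not stated. Two-sided is assumed, and one-sided is shown as a variant.

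**Step 1: scale of the contrast.** With a single-visit SD of 1, the SD of a change score is √(2(1 − ICC)) = √(2 × 0.5) = 1.0. At ICC 0.5 it therefore makes no difference whether d is standardised by the single-visit SD or by the change SD.

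**Step 2: power for α30 at 12 per arm.** The non-centrality is d√(n/2) = 1.0 × √6 = 2.449.

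| Calculation, two-sided | Power |
|---|---|
| Two-sample t on change, 22 df | 64.9% |
| Three-visit random-intercept model, (24 − 2) × (3 − 1) = 44 df | 66.9% |
| Normal approximation | 68.8% |

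A simulation of 20,000 trials gave 64.8%, 66.9% and 68.8% respectively. One-sided, the t test gives 76.7% and the normal approximation 78.9%.

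**Step 3: what 81% would take.** By the t calculation, 16 per arm gives 78.1% and 17 per arm 80.7%. At 12 per arm, the effect detectable with 80% power is d = 1.20 (80.2%).

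**Step 4: looking for the source of 81% at N = 24.** Two other analyses have a contrast variance of 0.75 instead of 1:
- ANCOVA always applied: 1 − 0.5² = 0.75.
- Average of the two follow-ups minus baseline, with d = 1.0 at both: 0.5 × (1 + 1/2) = 0.75.

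In each case the non-centrality is √6/√0.75 = 2.828. The normal approximation then gives 80.7%. With t it is 77.0% for ANCOVA (21 df) and 79.0% for the averaged contrast (44 df). Simulated ANCOVA with t gives about 75%. A one-sided normal calculation with 25 participants gives 80.4%.

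**Step 5: the 18 patients.** Two-sample t, two-sided, d = 0.97:

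| Reading | Power |
|---|---|
| 18 in total (9 per group) | 49.0% |
| Planned 12 per group | 62.2% |
| 18 per group (36 in total) | 80.7% |

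Seventeen per group gives 78.3%, so 18 is exactly the per-group answer. Other readings do not return 18: one-sided needs 14 per group, and a paired comparison needs 11.

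**Step 6: cross-check from the protocol's own second figure.** Required n scales with 1/d², so 18 per group at 0.97 implies 18 × 0.97² = 16.9, that is 17 per group, at d = 1.0. This agrees with Step 3.

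**Step 7: incomplete data (illustrative).** The 82% completion cited from an earlier study gives 0.82 × 12 = 9.8, about 10 per arm. The 16/24 threshold gives 8 per arm if losses are even.

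| Completers per arm | Change score, t | ANCOVA, simulated |
|---|---|---|
| 12 | 65% | 75% |
| 10 | 56% | 66% |
| 8 | 46% | 54% |

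**The case against.** The strongest reply is that the power sentence names no contrast, sidedness or N, so the simulation may have tested something else. This is partly right. With both follow-ups contributing and d = 1.0 at each, a simulated Wald test at 12 per arm gives 80.4–81.5%, and ANCOVA applied throughout gives 80.7% by normal approximation. A reader might infer from Step 2 that nothing at N = 24 yields 81% and that the simulation was miscalculated. The protocol does not support that inference. What stands is that these are different analyses from the one called efficacy, which is tied to 2 weeks alone, with baseline adjustment only if imbalance appears. They also need a normal approximation that is generous at this size.

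A second tempting inference is that d = 1.0 is too large because the quoted MBSR effect (0.3 to 0.4) should be taken off the psilocybin effect (1.29). The protocol makes no such subtraction. Nor does it suit this design: both arms receive MBSR, so under additivity its effect cancels.

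Third, 16/24 is a feasibility minimum for staying to study completion, and follow-up runs to 6 months. It does not forecast retention at 2 weeks. That is fair, so Step 7 is a sensitivity range and not an expected power.

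Fourth, the protocol says straight after the figure that estimation and feasibility are the main goals, and section 2.2 leaves efficacy differences to larger studies. Burnout is also a secondary outcome. This lowers the consequence, but it does not make either number correct.

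**Conclusion.** The point holds in this form. For the baseline-to-2-week contrast that the protocol defines as efficacy, 12 per arm gives about 65% power (65–69% by method), against a stated 81%: a shortfall of 12 to 16 percentage points. About 17 per arm would be needed. This rests on a two-sided 0.05 test, complete data, ICC 0.5 and d = 1.0. How the 81% was obtained cannot be established from the text, so it should be called a figure that does not describe the stated contrast, not a proven slip in calculation.

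The 18 is correct only per group. As printed it understates the total requirement by a factor of two, and the planned 12 per arm gives 62%.

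A reader might go further and conclude that the trial is too small for its purpose. The documents do not support that, because the stated purpose is a pilot. What is wrong is the printed claims, not the number of participants.

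**What to change.** Keep 24 participants and correct the text.

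- In both places where 81% appears, state about 65% power for the baseline-to-2-week treatment-by-time contrast at 12 per arm, two-sided 0.05, d = 1.0, ICC 0.5, complete data. Add that the effect detectable with 80% power is d = 1.2.
- Alternatively, make baseline adjustment unconditional and state about 75–77%. This changes the analysis text as well as the number.
- Whichever is chosen, name the N, sidedness and contrast. If the simulation used another contrast, say so and give the 2-week figure beside it.
- Add a sensitivity line for incomplete data: about 56% at 10 per arm and 46% at 8 per arm for change scores, or about 66% and 54% with ANCOVA.
- Replace 18 patients with 18 per group (36 in total), and add that 12 per group gives 62%.
- Reconcile the 25 in the Study Summary table with the 24 used elsewhere.

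The cost is a protocol amendment submitted to the IRB under section 15.8, and a less favourable printed figure. No patients, visits or procedures are added.
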